#### Settings, recruitment and retention plans

The study will be conducted through the West Virginia University (WVU) School of Nursing. Recruitment will take place through WVU Medicine, various rural counties, health providers or clinics, provider offices, public meeting centers, and religious groups throughout Appalachia. We will utilize effective strategies for identifying and recruiting research participants in rural Appalachia [35]. Our designated nurse for participant enrollment will use IRB-approved invitations and established enrollment protocols to prospectively identify potential participants. Additionally, personnel with IRB-approved access to patient records will conduct subject eligibility screening and initial recruitment contact in compliance with HIPAA requirements. Our recruitment materials, including notices, brochures, flyers, postcards, and presentations, will use IRB-approved wording. Additionally, patients referred for HF palliative care consultations will be invited to participate if they meet the study criteria.

Given the large clinical population, rural stakeholder involvement, and our past study enrollment, we are confident in our ability to recruit patients and family caregivers for this study. The trained nurse recruiters will remain blinded to group assignments until after the random allocation of each patient‒caregiver dyad and the signing of consent [37]. There may be delays in enrollment during winter (December to March) caused by road conditions and extreme weather in rural Appalachia. The PI and Co-I will oversee participant timelines, monitor, and report enrollment progress on a quarterly basis.

Research studies conducted on the long-term maintenance of palliative care programs have revealed key characteristics for success and sustainability. These successes include involving well-respected locals (e.g., rural stakeholders, faith community nurses) [38] and designing scientific-specific care programs for a significant health concern. Additionally, addressing family members’ needs and incorporating the cultural traditions of the population served helps maintain programs [24]. Sustainability is supported by the use of resources compatible with health equity in marginalized rural areas [39]. Other factors for sustaining programs are the use of means that are well suited to the area for sharing ongoing information (i.e., radio, newspapers, religious bulletins, veterans, and farmer meetings).

Notably, each of these characteristics, known to lead to sustainability in care over time, are, in fact, integrated into our intervention. The scientific premise is that the ability to sustain comes from components within the intervention itself [40]. This premise also serves as our guide for addressing some of the SDoH by integrating these within the intervention components. For example, using local nurses and volunteers reduces costs and enables patients’ direct access to regional HF care. We are also using visual inspection for older adults’ safe housing, using graphics/photos illustrating HF home care guides for low literacy, and sharing available rural services [20]. Furthermore, as in the framework guiding this study, the intervention bundle is grounded in social support, which aligns with the Appalachian concept of caring for neighbors [24].

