### Design/methodology

This study uses a randomized controlled trial (RCT) design stratified by sex to determine the effectiveness and helpfulness of the **HF**-FamPAL**home**CARE bundled intervention (N = 208, 104 dyads: 104 patients and 104 family caregivers). The intervention group (52 dyads) will receive the intervention. The control group (52 dyads) will receive attention control consisting of education on general health topics that indirectly affect HF (e.g., vaccinations, handwashing). At the end of the 12-month completion period, each group received the content provided to the other group. See Fig. 1.

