#### Randomization

The consulting statistician will use computerized randomization to generate numbers for subject enrollment. Two separate randomization lists will be created: one for males and one for females. Families will then be randomly assigned to either the control or intervention group at a 1:1 ratio. The group assignments are placed in sealed envelopes according to sex. Our RCT design adheres to CONSORT standards and rigorous research procedures [30]. The study is designed to enhance both internal and external validity, making it suitable for detecting differences between groups in behavioral intervention trials [31].

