#### Managing missing data

Our biostatistician will review and discuss strategies for handling missing data, including assessing whether data are missing at random or repeatedly missing, and these strategies will be reported in publications [45]. Any missing data will be identified early and collected within two weeks. Research staff will use secure REDCap or Qualtrics surveys for data entry, with parameters set to identify ranges to monitor for missing data. Data will be converted from REDCap/Qualtrics to SPSS/SAS on a weekly basis. Data will be tracked in real time for subject enrollment, withdrawal, and dropout. The CONSORT enrollment diagram will be updated biannually and reported in research team meetings. The consulting biostatistician will guide the use of intent-to-treat statistical approaches and appropriate imputation methods (e.g., mean replacement) for all patient and caregiver outcomes.

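### Recruiter blinding ends dyad by dyad, so nurses still recruiting may know earlier assignments; if the sex-specific lists are restricted, the next one is partly predictable

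*Protocol article*

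**What the plan says.** The section on settings, recruitment and retention states the rule: "The trained nurse recruiters will remain blinded to group assignments until after the random allocation of each patient‒caregiver dyad and the signing of consent". It describes the recruiting role in these terms: "Our designated nurse for participant enrollment will use IRB-approved invitations and established enrollment protocols to prospectively identify potential participants".

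The Randomization section gives the allocation method. On who generates the sequence: "The consulting statistician will use computerized randomization to generate numbers for subject enrollment". On stratification: "Two separate randomization lists will be created: one for males and one for females". On the ratio: "Families will then be randomly assigned to either the control or intervention group at a 1:1 ratio". On concealment: "The group assignments are placed in sealed envelopes according to sex". It gives no block size, does not say that a list must end balanced, and does not say who holds or opens the envelopes.

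The Design/methodology section plans 52 dyads in each group. The section on data collection for Aims 1 and 2 blinds the data collectors and uses different nurses for the two groups. Neither measure concerns what recruiters know about earlier families.

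**The concern.** The rule conceals the assignment of the dyad in hand and then releases it. Nothing else in the article keeps recruiters masked to past assignments while they approach the next family. Separate lists by sex serve a purpose only if each list is restricted in some way, because simple randomisation within each sex balances no better than one simple list. On a restricted list, the arm that has fallen behind is the more likely next assignment.

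Recruitment leaves room for discretion over whom to approach and when: clinics, provider offices, public meeting places, religious groups and referrals. A nurse who expects a particular arm next could, without intending it, time an approach or a consent visit accordingly. The groups could then differ in prognosis or motivation from the start. Intention-to-treat analysis keeps such a difference, and blinded data collection acts too late to prevent it.

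**Working it through.** The plan gives no figure on this point, so there is none to reproduce. The question is how predictable the next assignment would be under the list structures that the text allows.

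**Inputs from the protocol article.** 104 dyads, 52 planned per group (Design/methodology); 1:1 allocation from two lists by sex (Randomization).

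**Assumptions, not in the article.** The block sizes; the split by sex; a recruiter who knows all earlier assignments on the list and always guesses the arm with more places left (half credit at a tie); and a mean difference δ = 0.3 SD between families enrolled under opposite guesses.

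**Correct guesses.** For a list or block of 2m assignments forced to balance:

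expected correct = m + ½ × (4^m / C(2m, m) − 1)

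- Block of 2 (m = 1): 1 + ½ × (4/2 − 1) = 1.5 of 2, or 75.0%.
- Block of 4 (m = 2): 2 + ½ × (16/6 − 1) = 2.83 of 4, or 70.8%.
- Block of 8 (m = 4): 4 + ½ × (256/70 − 1) = 5.33 of 8, or 66.6%.
- List of 52 forced to 26:26 (m = 26): 26 + ½ × (9.08 − 1) = 30.04 of 52, or 57.8%.
- One list of 104 forced to 52:52 (m = 52): 52 + ½ × (12.81 − 1) = 57.9 of 104, or 55.7%.

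**Assignments known with certainty.** The expected number in a list or block of 2m is 2m/(m + 1). For blocks of 4 that is one third of 104, about 35.

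**Bias.** If the outcome mean shifts by ±δ/2 with the guess and p is the proportion guessed correctly, the expected difference between arms is δ × (2p − 1).

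| Assumed structure (104 dyads) | Correct guesses | Known with certainty | Bias at δ = 0.3 SD |
|---|---|---|---|
| Simple randomisation | 50% | 0 | 0 |
| One list forced to 52:52 | 55.7% | 2.0 | 0.3 × 0.114 = 0.03 SD |
| Two lists, 36:36 and 16:16 | 57.6% | 3.8 | 0.3 × 0.152 = 0.05 SD |
| Two lists, each 26:26 | 57.8% | 3.9 | 0.3 × 0.156 = 0.05 SD |
| Known blocks of 8 | 66.6% | 20.8 | 0.3 × 0.332 = 0.10 SD |
| Known blocks of 4 | 70.8% | 34.7 | 0.3 × 0.417 = 0.13 SD |
| Known blocks of 2 | 75.0% | 52.0 | 0.3 × 0.500 = 0.15 SD |

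The sex split hardly matters: 36:36 with 16:16 gives nearly the same result as two lists of 26:26. Block size, and whether the recruiter knows it, drives the answer.

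**The case against.** The strongest reply is that the quoted rule is ordinary allocation concealment. Learning an assignment after the event does no harm unless the sequence is restricted in a way that recruiters can track, and the article states no such restriction. Block size and custody of the envelopes are details that an article commonly leaves to the full protocol. This stands: their absence is no fault, and the point rests on the stated rule alone.

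The table is also an upper bound. The article speaks of nurse recruiters in the plural, gives eligibility screening and first contact to staff with access to records, who are not said to learn assignments, and takes referrals from outside. No one is said to see both full sequences. This stands too.

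A reader might make four stronger inferences that the documents do not support:

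- *That the lists must be restricted, because simple randomisation of 104 dyads gives exactly 52:52 only 7.8% of the time.* The figure is right (C(104, 52)/2^104 = 0.078), but 52 is a planned group size, not a stated property of the lists.
- *That the type I error rises to between 12% and 24%.* Those values need known blocks of 2, differences of 0.3 to 0.5 SD, every enrolment steered by the guess, and a simple t-test. The plan is a repeated-measures mixed model with a baseline measurement. A shift equally present at baseline cancels from contrasts of change from baseline. A difference in motivation or in speed of decline, which alters the later course, would not cancel.
- *That this is an open trial with envelopes in the field.* The article says neither; it describes an attention control and blinded data collectors.
- *That self-reported outcomes make this worse.* Self-report bears on bias in measuring outcomes, not on who is enrolled.

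**Conclusion.** The concern holds as a conditional risk created by a stated rule. Recruiter blinding ends after each dyad's allocation and consent, and nothing in the article masks recruiters to earlier assignments. With restricted lists, correct guessing rises from 50% to about 58% if each list is only forced to balance, and to about 67% to 75% with small fixed blocks known to the recruiter. With simple randomisation there is no excess.

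The bias is probably small: about 0.05 SD at 58% and 0.13 SD at 71%. Both values rest on the assumed 0.3 SD difference and on a recruiter with full knowledge who acts on every guess. The documents do not show that the next assignment can in fact be guessed. They do fix a rule whose safety depends on a list structure they do not give, whereas masking recruiters throughout is safe under any structure. This is a cheap improvement worth making, not a demonstrated flaw in the trial.

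**What to change.** In the section on settings, recruitment and retention, replace the rule with one under which nurse recruiters remain blinded to all group assignments throughout enrolment.

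In the Randomization section, state that someone who does not recruit (the statistician or an arm-specific nurse) holds the envelopes, and opens each only after both consents are signed and both baseline questionnaires are complete. This also settles the order of consent and allocation, since the present sentence names allocation first. The arm-specific nurse, already separate for each group, then tells the family its assignment.

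The cost is a wording change and a hand-over step, with no extra participants. The downside is that the recruiter can no longer give the family its assignment. Moving from envelopes to a REDCap randomisation function is optional: the article names REDCap for data entry only, and sealed envelopes are acceptable if recruiters do not handle them.

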### Interventions

#### Standard care group

Participants in both groups will receive standard care, which is routine HF instruction at primary providers or specialist clinic appointments. Current standard HF instruction often has neither home HF skill-building, few home care instructions designed for family caregivers, nor EOLPC discussions. Standard care includes materials routinely given to all patients to achieve the national Joint Commission and AHA core HF standards for symptom management, support transitional care, and prevent 30-day readmission [41]. For time and attention control, the control subjects received instructions concerning handwashing techniques, vaccinations (e.g. Flu), and fraud prevention.

#### The HF-FamPALhomeCARE intervention bundle group

This study uses implementation science to deliver the verified evidence-based intervention bundle to the underserved population in rural Appalachia [39]. The **HF**-FamPAL**home**CARE intervention is a bundle of empirically verified preliminary HF trials [15] aimed at improving home HF palliative care via Appalachian-centered cultural approaches, engaging faith community nurses, and visiting volunteers to diminish health disparities and address the SDoH in rural Appalachia. The nurse interventionists in this RCT are experienced in arranging free travel to available rural/regional health care and WVU specialty care and are trusted by the medically underserved Appalachian population [42]. The nurse interventionist will select and train local volunteers to assist with home visits and telephone contacts. The intervention group will receive 5 biweekly sessions, which include two home visits (delivered by a team consisting of a faith community nurse and a visiting volunteer) and three biweekly telephone calls on HF home care, home safety, caregiver burden, and practical skills related to home EOLPC care.

We will use coaching and teach-back conversations during each intervention session to verify the understanding of HF education materials and practice home care skills [35]. Affirmations, positive statements, are used at the end of each session to encourage patients and their family caregivers to promote self-belief and motivation in HF home care [43]. For example, *“I will practice my skills to recognize HF symptoms, ways to improve fatigue, anxiety, and depression, and will report symptoms to the healthcare provider.”* Additional booster reinforcement sessions via telephone calls will be provided at 3, 6, 9, and 12 months to allow participants to practice home HF care skills and ask questions.

#### Treatment fidelity and quality assurance procedures

A comprehensive intervention manual with guiding scripts has been created. It includes strategies from previous family HF studies to facilitate **HF**-FamPAL**home**CARE discussions with each dyad. This manual will also help nurses build rapport by including content to address the anticipated needs and concerns of patients and family caregivers. Based on past trials and training roleplay, coaching sessions typically last between 60 and 120 min. Nurses are trained on using the **HF**-FamPAL**home**CARE manual and are advised to spend 30 min preparing for each session by reviewing session content [35]. Fidelity observations will be conducted and reported, with a positive fidelity rating achieved through consistent delivery of the intervention [44].

### Data collection procedure

#### Data collection for Aims 1 & 2

Data will be collected separately from all patients and caregivers at baseline and at 3, 6, 9, and 12 months. We will collect sociodemographic variables such as sex, age, race/ethnicity, comorbidities, and other social determinants of health (e.g., income adequacy, health insurance, education, health care services used, safe housing for older adults, etc.) at baseline. To decrease the risk of diffusion of treatment to the controls, the nurse interventionists working with families in the intervention group will be different from the nurses working with the control group. Those collecting data will be blinded to the group. Secure data collection and storage will be maintained. A HF home care checklist is used to assess the home care skills learned by the caregiver at 3, 6, 9, and 12 months and to identify areas that may need reinforcement. The interventionists and the participants in the intervention group completed separate anonymous helpfulness rating scales at 6 and 12 months to determine the helpfulness of the intervention bundle.

#### Data management and quality assurance

Data management protocols and an audit trail of the data management decisions will be kept for quality assurance and data integrity. Guides for verifying data and analyzing data distributional features and group equivalencies at the baseline will be followed [45]. Preliminary analysis will be conducted to verify that the statistical assumptions are met and whether transformations are needed. Differences in demographics between participants and those who declined to participate were reported. The reasons for declining to participate will be recorded.

To enhance the transparency and reproducibility of the research, the deidentified dataset, project data descriptions, and statistical models generated by R01 are shared [46]. These data will be shared in the appropriate NIH repository of the National Archive of Computerized Data on Aging (NACDA) hosted by the Inter-university Consortium for Political and Social Research (ICPSR). A description of the data management plan will also be submitted.

#### Managing missing data

Our biostatistician will review and discuss strategies for handling missing data, including assessing whether data are missing at random or repeatedly missing, and these strategies will be reported in publications [45]. Any missing data will be identified early and collected within two weeks. Research staff will use secure REDCap or Qualtrics surveys for data entry, with parameters set to identify ranges to monitor for missing data. Data will be converted from REDCap/Qualtrics to SPSS/SAS on a weekly basis. Data will be tracked in real time for subject enrollment, withdrawal, and dropout. The CONSORT enrollment diagram will be updated biannually and reported in research team meetings. The consulting biostatistician will guide the use of intent-to-treat statistical approaches and appropriate imputation methods (e.g., mean replacement) for all patient and caregiver outcomes.

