#### Sample size

The power and sample size determination is based on a preliminary RCT, which revealed a moderate effect reduction in the burden of caregiving and improvements in patients’ HF-related health status [15]. With the use of G*Power v.3.1.9.7 for repeated-measures ANOVA with α = 0.05, Cohen’s d = 0.25 (moderate effect size), a power of 80%, two groups with 5 measurements, and correlations among repeated measures (0.50), a *sample size of 86 family dyads* will be needed. Our power analyses performed by this study’s statistician indicate that this sample size is sensitive enough to detect a significant difference in the study outcomes with this repeated measure design [36].

Our biostatistician’s revised precision calculation for linear mixed model analysis was based on the effect size outcomes of our HF palliative care studies. To account for an expected 20% attrition (many due to HF-related deaths), eight additional families will be recruited for each group. The calculated sample size was 86 patients, with an additional n = 18 for the expected 20% attrition rate (total sample N = 208; 104 patients and 104 caregivers) for this study. In this analysis, the random and fixed effects and quarterly repeated measures also add power.

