### Data analyses

All the outcome measures have established discriminant or construct validity, internal consistency, reliability, and specificity. Each has been used with diverse populations, chronic illness patients, and HF families. These measures have been shown to distinguish clinically significant differences and are responsive to changes over time. These questionnaires were easily completed within 30 min. The sample demographics will be tabulated and reported.

#### Data analysis for Aims 1 & 2

Our experienced statistician will employ hierarchical generalized linear models with repeated measures to identify significant differences in outcomes between groups and to control for nested dyadic analysis [49]. The models will include fixed effects of treatment, time, and the treatment‒time interaction. Patient and family caregiver effects will be treated as random to account for dependence among repeated observations on the same subject as well as among subjects within the same family [37]. These models detect changes in outcome variables over time, differences between groups, and within-group differences over time. The SAS Proc MIXED procedure will be utilized. General linear modeling using linear contrasts of selected model parameters will test for significant differences. Point estimates and confidence intervals will be produced via contrasts and estimates of appropriate linear combinations of model parameters. The overall experimental error rate will be controlled via the Bonferroni procedure for multiple testing.

Multicollinearity among study variables will be determined and statistically controlled for in the data analysis. The number of mental health visits (for severe anxiety and depression) will be tracked for comparison between groups. To assess differences in HF EOLPC decisions, the number of family members and patients who sign an advance directive form, reveal a decision, or identify someone to help with HF EOLPC options will be recorded and reported. The proportion of patients signing an advance directive form will be used to evaluate the acceptability of EOLPC discussions. Subjects’ outcomes will be recorded at the time of death or 12 months postintervention, whichever comes first.

#### Data Analysis for Aim 3

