## Limitations and alternatives

The population of West Virginia is 93% Caucasian, but we have successfully enrolled underrepresented minorities in past studies. We anticipate a 20% attrition rate, primarily due to HF-related deaths. In previous studies, few caregivers withdrew after patient death, indicating that they were able to contact study nurses. To increase enrollment, program brochures are distributed in local churches by lay ministers and faith community nurses. Additionally, healthcare providers involved in HF patient discharges or ER visits may refer families to the program. Finally, the West Virginia University (WVU) integrated data repository (IDR) will be used for enrollment, as it has proven helpful for screening patients with HF across WV counties in the PI’s previous trials.

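### Mean replacement is the only example given of an appropriate imputation method for all outcomes; used on missing scores, it understates the standard error or shrinks the effect, and the planned mixed model does not need it

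*Protocol article*

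**What the plan says.** The protocol article, under Managing missing data, states: "The consulting biostatistician will guide the use of intent-to-treat statistical approaches and appropriate imputation methods". The parenthesis and scope that follow are "appropriate imputation methods (e.g., mean replacement) for all patient and caregiver outcomes". No other imputation method is named. The same section says the biostatistician will consider strategies for missing data and assess whether data are missing at random.

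Attrition is given twice. Limitations and alternatives says "We anticipate a 20% attrition rate, primarily due to HF-related deaths". Sample size has "expected 20% attrition (many due to HF-related deaths".

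For Aims 1 and 2, the Data analyses section plans repeated-measures models with random patient and caregiver effects: "The SAS Proc MIXED procedure will be utilized". On death, it says only that "outcomes will be recorded at the time of death or 12 months postintervention, whichever comes first". It gives no rule for scores that would have been due at visits after death.

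**The concern.** Replacing a missing score by a mean enters a constant as if it had been observed. The damage depends on which mean is used, and the protocol does not say.

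- **Arm mean.** The difference between arms equals the observed-data difference, but the variance is too small and the sample size is counted as if complete. Tests reject too often and intervals are too narrow.
- **Mean over both arms.** Every filled value is the same in both arms, so the estimated difference is pulled towards zero.

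Neither version adds information. A mixed model fitted by likelihood already uses every observed visit and is valid under missing at random without filling anything in.

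The expected cause of attrition adds a second problem. A quality-of-life, depression or anxiety score after death does not exist. The stated scope covers all patient outcomes, with no exception for deaths. At stake are the scale scores in Hypotheses 1a, 1b, 2a and 2b.

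**Working it through.** The plan gives no figure for the effect of imputation, so there is none to reproduce. The check does not depend on the sample-size calculation, apart from the correlation taken from it.

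**Inputs from the protocol.** 52 dyads per arm (Design/methodology); 20% attrition (Sample size; Limitations and alternatives); "two groups with 5 measurements, and correlations among repeated measures (0.50" (Sample size); assessments at baseline, 3, 6, 9 and 12 months.

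**Assumptions.** SD 1, equal attrition in both arms, data missing completely at random, all 20% missing by 12 months, and an illustrative true effect of 0.50 SD. The protocol gives no SD and no attrition by arm.

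**1. Arm-mean replacement, one visit.** Let n be the number randomised per arm and m the number observed. After filling, the reported variance of an arm mean is (m−1)s²/[(n−1)n]; the true variance is s²/m. The ratio of reported to true SE is √{m(m−1)/[n(n−1)]}, close to 1−q for a missing share q.

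- With n = 52 and m = 42 (10 missing): √(1722/2652) = 0.806. The effective critical value is 1.96 × 0.806 = 1.58, so type I error is 0.114.
- With q = 0.20 exactly: ratio 0.80, critical value 1.568, type I error 0.117.
- Simulation of 10,000 runs: mean reported SE 0.175 against a true SD of 0.215; type I error 0.108. Observed data only: SE 0.217, type I error 0.045.
- Simulation of 4,000 runs: type I error 0.119 with arm means and 0.049 with observed data only.

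**2. Overall-mean replacement, one visit.** Both arms receive the same constant for a share q, so the expected difference is (1−q)δ = 0.80 × 0.50 = 0.40 SD. Simulation gives 0.402, against 0.498 from observed data. With no true effect, type I error is 0.0515.

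**3. Five visits, correlation 0.50, arm means by visit, no true effect.**

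| Missing pattern and analysis | Contrast | Type I error |
|---|---|---|
| Gradual dropout to 20%, complete-data contrast | 12 months alone | 0.118 |
| Same | Average over follow-up | 0.086 |
| Same | Average change from baseline | 0.056 |
| Missing 0/5/10/15/20%, random-intercept model | 12 months | 0.105 |
| Same | Change from baseline | 0.089 |
| 20% missing at every follow-up visit, random-intercept model | 12 months | 0.110 |
| Same | Change from baseline | 0.101 |

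Observed-data generalised least squares, with variance components taken as known, gave 0.053 for the 12-month contrast and 0.048 for change from baseline.

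The inflation is therefore smaller when dropout builds up gradually and the contrast uses baseline or averages visits. It approaches the single-visit figure when the full 20% is missing from the first follow-up visit.

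**The case against.** The strongest reply is that the protocol fixes no imputation method. Mean replacement appears once, as an example, under a statistician who is to judge what is appropriate and to look at the missingness mechanism. The likelihood mixed model is already the planned analysis, and no sentence says filled-in values will be fed into it. The level of the mean is not stated either; for questionnaires it could mean a person's own mean over the items of a scale. All of this is fair, and it limits the point to a conditional one. It does not remove it: the scope given is outcomes, not items, and this is a method put forward as suitable, not a detail left for an analysis plan.

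Four stronger readings are tempting and are not supported.

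- **That patients who died will be given survivors' averages.** The missing-data section does not mention death, and the sentence on recording outcomes at death can be read as ending assessment there. The text permits filling in after death; it does not plan it.
- **That the false-positive rate more than doubles throughout.** That holds for the isolated 12-month comparison, and nearly so where the full 20% is missing from the first follow-up. With gradual dropout the other contrasts give about 0.06 to 0.09, and overall means do not inflate it under equal random dropout.
- **That unequal dropout of sicker patients makes mean replacement biased in itself.** With 30% and 10% missing by arm, arm-mean filling gave −0.10 SD under no effect and type I error 0.166. The unadjusted observed-data comparison also gave −0.10 SD, with type I error 0.077. Filling worsens the error rate; it does not create that bias.
- **That 20% applies equally to caregivers.** The attrition is tied mainly to patient deaths, and Limitations and alternatives reports that few caregivers withdrew after a death in previous studies.

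The absence of named sensitivity analyses for dropout and death is no fault here, since an analysis plan may set them.

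**Conclusion.** The point holds in conditional form. The one imputation method the protocol offers is unsuitable for missing outcome scores in this trial and redundant beside its own model. If arm means are used, the reported SE at a visit with 20% missing is about 0.80 of the true one. Type I error is then about 0.12 for the 12-month comparison and, with gradual dropout, about 0.06 to 0.09 for change-from-baseline or averaged contrasts. If overall means are used, type I error stays near 0.05 but a 0.50 SD effect is reported as about 0.40 SD.

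These sizes rest on 52 per arm, correlation 0.50, equal attrition and data missing completely at random; the 0.50 SD effect is illustrative. The timing of dropout changes the size of the arm-mean inflation, not its direction. The missing exemption for death is a gap in wording that allows a meaningless score, not evidence that one is planned. Severity: should be fixed before analysis.

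**What to change.** In Managing missing data, delete the parenthetical example and state:

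- The primary analysis of the Aim 1 and 2 scale scores is the likelihood-based mixed model already planned under Data analyses, fitted to all observed scheduled assessments without single imputation of outcome scores.
- No score is imputed for a visit after death.
- Missing items within a scale follow that instrument's scoring manual.
- If imputation is used as a sensitivity analysis, it is multiple imputation.

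The choice of sensitivity analyses for dropout and death can be left to the SAP. It should say there how the patient comparison is to be interpreted when some patients die, because leaving post-death visits empty in a mixed model does not by itself settle that question.

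The cost is one paragraph, with no new data and no change to the main model.
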